#### Adoption:

How success the telecare consultation adopted at the staff and clinic level will be determined by the Readiness for Implementation Model Survey [32]. The survey comprises 42 items asking the healthcare providers about the facilitators and barriers of adopting telecare in GOPC. The scores range from 0 to 100, with higher scores indicating better adoption. The scale has demonstrated good inter-rater reliability [32].

In addition to quantitative survey, separated semi-structured group interviews with healthcare providers and patients will be conducted to explore their views on facilitating, hindering factors, and the feasibility of implementing the program in GOPC.

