## Conceptual framework

The hybrid effectiveness-implementation design of this study is guided by two models. The design of the implementation strategies is informed by the Generic Implementation Framework (GIF) [18], while the design of the effectiveness and implementation evaluations is based on the RE-AIM framework [19].

The GIF proposes that there are facilitating and hindering factors, and strategies influencing each stage of implementation process, namely, development and exploration, preparation, operation, sustainability phases [18]. Facilitating factors such as support from management level and hindering factors such as low staff engagement level may support or hamper the dissemination and implementation process of the program. The present study will therefore utilise the GIF as a foundation, and address the facilitating and hindering factors by providing appropriate implementation strategies, such as staff training and program orientation, in different stages of the implementation process.

RE-AIM is an evaluation framework to guide the effectiveness and implementation outcomes evaluation [19]. RE-AIM examines 5 dimensions: *Reach* into the target population, *Effectiveness* of the intervention, *Adoption* by the staff and setting, *Implementation* fidelity, and *Maintenance* (i.e. degree of sustainment over time). Thus, RE-AIM is ideal for structuring the proposed hybrid implementation-effectiveness evaluation. The results of these evaluations are expected to lead to more profound insights in the feasibility and translatability of the intervention, optimal training for the staff and patients, and the factors influencing the acceptance of the intervention by the target population.

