## Aims

There are two aims for the present study: 1) compare the clinical effectiveness between alternate telecare and face-to-face consultations and usual face-to-face consultations in improving client outcomes (i.e. HbA1c, Body Mass Index [BMI], fasting lipid profile, medication adherence, quality of life [QoL]) and health service utilization (i.e. unscheduled attendance at general practitioners’ office, emergency department, general out-patient clinic) among DM patients, and 2) explore and identify whether an implementation strategy of alternate telecare and face-to-face consultations at general out-patient clinics is reachable to the target DM patients, adoptable to the clinic staff and clinic, implementing accurately, and sustainable in long term.

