## Discussion

The purpose of this study is to investigate both the implementation and effectiveness outcomes of a telecare consultation program on long-term care services for DM patients in Hong Kong. Although there has been an adequate amount of research looking into the clinical effectiveness of telecare on DM care, these studies have shown weaknesses in considering the barriers and obstacles in implementing telecare in a real-world setting. Aiming to bridge this very gap, our proposed study may be insightful and inspiring for future adaptation of telecare in diverse chronic disease managements in Hong Kong primary care settings.

Throughout the program, the intervention group will be attending a total of 7 alternate virtual and face-to-face consultations within 84 weeks, while the control group will be having complete conventional face-to-face consultations. Clinical outcomes such as BMI, blood glucose level, fasting lipid profile, and most importantly HbA1c will be measured and compared at three distinct time points. Simultaneously, implementation strategies of telecare consultation will be evaluated in the aspects of the reach into the target population, adoption by the staff and setting, implementation fidelity, and maintenance as guided by the RE-AIM framework. To the best of our knowledge, this study is the pioneering attempt in Hong Kong to adopt a hybrid design to examine outcomes and effects. The strength of this study include the fact that the program has been receiving unlimited supported by the key stakeholders, including the managerial level and frontline staff of general out-patient clinics. The implementation and logistic protocols, training workshops, and the provider guidelines were co-designed by the research and the service teams. The proposed telecare consultation model is thus more likely to be sustained in reality, since it is built with the engagement of the service partner.

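### The Adoption outcome is scored by a provider readiness survey, which cannot by itself show whether staff and clinics took telecare up

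*Protocol article*

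**What the plan says.** The second aim in the protocol article (Aims) includes whether the strategy is "adoptable to the clinic staff and clinic, implementing accurately, and sustainable in long term". The Discussion lists the implementation outcomes as separate dimensions: "adoption by the staff and setting, implementation fidelity, and maintenance as guided by the RE-AIM framework".

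The section on Adoption fixes how that dimension is measured:

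- Instrument: "How success the telecare consultation adopted at the staff and clinic level will be determined by the Readiness for Implementation Model Survey".
- Content: "The survey comprises 42 items asking the healthcare providers about the facilitators and barriers of adopting telecare in GOPC".
- Reading of the score: "The scores range from 0 to 100, with higher scores indicating better adoption".
- Second source: group interviews with providers and patients, meant to "explore their views on facilitating, hindering factors, and the feasibility of implementing the program in GOPC".

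No other measure is given under Adoption.

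**The concern.** Readiness, and the conditions that help or hinder a service, come before uptake. They may predict it, but they are not uptake. The section nevertheless takes a score built on perceived conditions and reads it as the degree of adoption achieved.

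At stake is what the trial can conclude on its second aim. In a type 2 hybrid design, the implementation side is tested alongside effectiveness, so this aim is not incidental. Two clinics whose providers hold similar views would receive similar Adoption scores even if telecare were shared among all providers in one and carried by a single provider in the other. That difference matters to a service deciding whether to extend telecare, and the stated outcome is not designed to show it.

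**Working it through.** The protocol gives no figure to reproduce on this point. The check sets its sections side by side, and a little arithmetic gives the scale.

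**1. Determinant or outcome?** The Conceptual framework uses two models. The implementation framework supplies facilitating factors (management support is the example) and hindering factors (low staff engagement is the example) that act on the implementation process. RE-AIM supplies the outcomes, and adoption by staff and setting is one of them. Study design makes a similar distinction between evaluating the implementation strategies and determining the factors that may affect the process. The survey, as described under Adoption, asks about the first kind of quantity, and its score is assigned to the second. The only measurement property cited for it there is inter-rater reliability, which concerns agreement and does not show that the score tracks uptake.

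**2. Does another measure supply uptake by staff or clinic?**

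| Section | What is recorded | Stated by provider or clinic? | Enters Adoption? |
|---|---|---|---|
| Reach | Patients eligible, invited, excluded, enrolled | No | No |
| Adoption, interviews | Views on factors and feasibility | No count of delivery | Yes, as views |
| Implementation, checklist | Whether the workflow was followed | No | No |
| Implementation, 5% documentation check | Provider adherence to the protocol | No | No |
| Maintenance | Patients who withdraw or ask to change mode, with reasons | No | No |

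**3. How much delivery information exists?** Inputs are seven consultations with the first onsite (Operation phase), 350 patients per group and 20% drop-out (Sample size), and seven clinics (Study setting). Strict alternation after the first visit is an inference; it puts telecare at visits 2, 4 and 6.

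- Planned telecare consultations: 350 × 3 = 1,050. Per clinic, with even recruitment: 1,050 / 7 = 150.
- Counting only patients who complete: 350 × 0.80 = 280, and 280 × 3 = 840, or 840 / 7 = 120 per clinic.

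**4. Could the 5% check stand in?** The unit sampled is not stated, so two readings are shown, each assuming an even spread over clinics.

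- 5% of patients: 0.05 × 700 = 35, and 35 / 7 = 5 per clinic. About half, two or three, would be in the telecare group.
- 5% of telecare consultations: 0.05 × 1,050 = 52.5, and 52.5 / 7 = 7.5 per clinic.

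On either reading this is too few to estimate an uptake rate for a clinic, and fewer still for a provider.

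**5. Which delivery measure suits this design?** Patients are individually randomised to the consultation mode, and the same providers serve both groups. Suppose a clinic has k eligible providers (k is not given). The proportion of providers with at least one telecare consultation reaches 100% once k of the roughly 150 planned consultations have been held, one by each. That measure would probably sit near its ceiling and mostly reflect allocation. Delivered over planned uses every planned consultation, so allocated volume is in the denominator. The spread across providers separates shared delivery from concentrated delivery.

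**The case against.** The strongest reply is that the trial, not the clinic, determines how much telecare is delivered. Providers do not freely choose it, because the assigned patient's schedule calls for it. In that setting, providers' views on what helps and hinders are a reasonable way to study whether the strategy could be adopted, and the aim is worded as adoptability. This stands in part. It justifies keeping the survey and interviews, it rules out a simple at-least-one-consultation measure, and it means any delivery figure describes uptake under trial conditions. It does not rescue the sentence that reads a higher score as better adoption, because the protocol's own framework separates the two.

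A reader might also infer that a clinic could deliver almost no telecare, be reported as a high adopter, and go unnoticed. The documents do not support that. The checklist, the documentation check, the mode-change counts and the documented bimonthly meetings could all bring poor delivery to light, and the RE-AIM dimensions are evaluated together. The gap is that none of these is stated to be reported by provider or clinic or to inform Adoption.

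Two further inferences go too far. One is that survey scores will be high from the start because "the program has been receiving unlimited supported by the key stakeholders, including the managerial level and frontline staff of general out-patient clinics". That is a general statement in the Discussion with no score behind it, and the Conceptual framework itself names low staff engagement as a possible obstacle. The other is that no survey item concerns delivery. The items are not shown, so the point rests on the survey's name and its description in the article. The number of clinics approached is likewise a detail that a condensed article may leave to the full protocol.

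**Conclusion.** The point holds as a mismatch between measure and outcome. The protocol fixes both the instrument and its interpretation, so this is not a detail left to a fuller document. Followed as written, the plan would report perceived conditions as achieved adoption.

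The size cannot be stated as a bias, because no numerical target or threshold for Adoption is given. Its scale is that up to about 1,050 planned telecare consultations (840 counting completers only) would show where and by whom telecare was delivered, and none is planned to be summarised for that purpose. These counts assume alternation from the second visit, and the per-clinic figures also assume even recruitment. The conclusion depends on neither. It does depend on the survey being as the article describes it.

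The consequence is confined to the second aim. The non-inferiority comparison on HbA1c is untouched. The change is worth making because it is cheap and alters what can be concluded about adoption.

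**What to change.** 1. Keep the survey and the interviews, and label them as measures of readiness and determinants.
2. Remove the statement that a higher score indicates better adoption.
3. Report under Adoption the share of planned telecare consultations in the telecare group that were actually delivered by telecare, by clinic, and how the delivered ones were spread across eligible providers.
4. Do not use the proportion of providers with at least one telecare consultation as the Adoption outcome.
5. State that these figures describe uptake under trial conditions, since randomisation sets the planned volume.

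The cost is a wording change and a tally from existing consultation records, with no new patient contact. Reported adoption may turn out less favourable than the survey score alone would suggest.

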#### Implementation:

A performance checklist that developed by the PI according to the workflow of the program will be used to identify whether the program is implemented as intended. The checklist was validated by a group of healthcare professionals such as doctors, optometrists, and nurses, and global researchers who have experience in conducting implementation science studies. In addition, five percent of the patient documentation will be extracted from the database of the hospital to check the adherence of the interventions by the healthcare providers to the set protocol.

#### Maintenance:

The sustainability effect of the program will be evaluated by measuring the effectiveness outcomes at 84 weeks after the commencement of the program. At each data collection timepoint (i.e. baseline, 42 weeks, 84 weeks), the RAs will record the number of patients who withdraw from the program or request to change from alternate telecare and face-to-face consultation to usual face-to-face consultation or vice versa and the reasons for doing so. In addition, maintenance of the program will depend on the costing evaluations. The cost of telecare consultation, including the software and on-going costs, will be estimated from the provider perspective as well as from a societal perspective, including patients’ costs in terms of travelling and time. An ingredient approach will be employed to estimate the cost. The total estimated cost for both groups will be estimated and compared.

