### Study setting, subjects and recruitment strategies

The study will be implemented in seven government out-patient clinics (GOPCs) under Hospital Authority in the New Territories West Cluster from Jan 2023 to Dec 2025. The subjects who are DM patients (either type 1 or type 2) with regular follow-up appointment in the clinic will be screened and recruited into the study if they 1) are aged 18 or above, and 2) have a confirmed diagnosis of diabetes. They will be excluded if they are 1) having dementia, 2) having unaccompanied hearing or visual loss, 3) not living in an area with Internet coverage.

Research assistants (RAs) will introduce the program to the eligible DM patients in the clinics. For those who are eligible and agreed to join, RAs will collect their signature for the consent form and baseline data. After successfully collect their data, the RAs will call the principal investigator (PI) of the research team for randomization. The PI will put the numbers (i.e. 1 = “telecare group”, 2 = “control group”) that generated from a software “Research Randomizer” into sealed envelopes and open sequentially when receive the call from RAs. A block randomization of size 8 will be employed to ensure balanced representation of the subjects in each group. The PI will provide the group list to the clinic clerk, who will then inform individual participants about their randomization results and guide them to follow the assigned delivery consultation mode. The Research Assistants (RAs), who will solely be involved in data collection, and the statistician, who will be responsible for data analysis, will be blinded to the group assignment.

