#### Effectiveness:

The effectiveness outcomes of the program include HbA1c, fasting lipid profile, body mass index (BMI), medication adherence, quality of life (QoL), and health service utilization. The primary effectiveness outcome of this study is the HbA1c level. HbA1c is a standard assessment of glycemia and refers to the mean blood glucose levels over the previous 2 to 3 months [27]. Fasting lipid profile includes cholesterol level, and high- and low-density lipoprotein. Similar to HbA1c, the fasting lipid profile will be drawn from patients’ blood when the patient has onsite consultation. The results can be extracted from the hospital database. BMI will be measured each time during GOPC admission by dividing weight in kilograms by height in meters^2^. Medication adherence will be measured by adherence to refills and medication scale [28]. This 4-point Likert scale has scores range from 12 to 48, with lower scores representing better medication adherence. The scale has demonstrated high internal consistency, with a Cronbach’s alpha of 0.81 [28]. Quality of life will be evaluated by the version 2 of the 12-item Short Form Health Survey [29]. The scale measures various aspects of physical and mental health from which physical and mental component scores can be summed. It has been widely used in Chinese diabetic patients with good validity and reliability [30,31]. The outcomes of health services utilisation include the total number of unscheduled visits to general out-patient departments, general practitioners (GP), emergency departments, and hospitals, and the total health service attendance. The information will be extracted from the hospital database, except for GP visits, which will be reported by the subjects.

Background demographic data will be collected to compare the baseline differences between the two groups. They include age, gender, marital status, education, work status, years of using a smartphone, financial status, family living in the same household, caretaking support, diabetes type and duration, date of first follow-up, number of referrals, professionals to whom the patient is referred.

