### Data collection

Data will be collected at three time-intervals, baseline pre-intervention (T1), 42 weeks (T2), and 84 weeks after the interventions begin (T3). The RAs, who are blinded to group allocation and not involved in interventions, will collect the data in the GOPCs in T1, and *via* telephone call in T2 and T3. They will be tested on inter-rater reliability to ensure data quality. Five percent of the data will also be randomly selected for independent review. Participants will receive a HK$ 50 coupon as a token of appreciation for their time commitment and to help cover transportation costs upon completion of the T3 data collection.

Semi-structured interviews will be carried out in T3 by research team members. A one-time in-depth focus group interview allows the research team to understand the group dynamics where different opinions from persons can be explored. During the interview, participants will be asked questions such as "What is your experience with the telecare consultation?" and "What aspects of the intervention program do you like or dislike?" At each time point, separated interviews will be conducted to the same group of people including (1) GOPC manager, (2) clinic healthcare providers (i.e. doctor, nurse), and (3) 64 (20%) of the patients in telecare group.

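### The research assistants declared blind also record requests to change consultation mode, so their blinding cannot be relied on for patients who ask to switch

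*Protocol article*

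**What the plan says.** Under Study setting, subjects and recruitment strategies, the RAs are described as staff "who will solely be involved in data collection", and they and the statistician "will be blinded to the group assignment". Allocation is meant to reach the patient by another route: "The PI will provide the group list to the clinic clerk, who will then inform individual participants about their randomization results". The Data collection section repeats the claim: "The RAs, who are blinded to group allocation and not involved in interventions, will collect the data in the GOPCs in T1". It adds that the same RAs collect the T2 and T3 data by telephone.

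The Maintenance section gives the RAs a further task. At baseline, 42 weeks and 84 weeks, "the RAs will record the number of patients who withdraw from the program or request to change from alternate telecare"; the change may be "to usual face-to-face consultation or vice versa and the reasons for doing so".

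Under Effectiveness, the outcomes include a medication adherence scale, the SF-12 version 2 and health service use. HbA1c and lipids come from blood drawn at onsite visits, with results taken from the hospital database. Service use also comes from that database, "except for GP visits, which will be reported by the subjects".

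**The concern.** A request to leave one consultation mode for the other names the mode the patient was assigned. Whoever takes down the direction and the reason learns that patient's arm. The protocol gives this task to the staff it declares blind, at the timepoints when they collect outcomes. No section assigns the record to other staff or places it after the outcome questions.

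At stake is the recording of outcomes that depend on patients' answers in the telephone calls. An interviewer who knows the arm may prompt or record differently. The Hypothesis section expects no differences between groups in client and service-use outcomes, so such a bias could hide a telecare deficit as easily as create a false difference.

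**Working it through.** **Consistency of the text**

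- Study setting and Data collection: the RAs are blind, and they collect outcomes by telephone at T2 and T3.
- Maintenance: the same RAs record change requests, their direction and the reasons at each timepoint.
- Baseline: the RAs call for randomisation only after the baseline data are collected, so no change of mode can be requested before then. Only T2 and T3 matter.
- Patients exposed: those who request a change in either direction, and possibly those who withdraw for a reason tied to the mode. For all other patients the record reveals nothing.
- Outcomes exposed: adherence, SF-12v2 and GP visits. Laboratory and database outcomes do not depend on the RA call.

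**Possible size**

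The protocol has no figure of its own to reproduce here, and it gives no expected rate of change requests. A range is therefore assumed.

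Inputs:
- Analysed per arm: 350 × (1 − 0.20) = 280, from the Sample size section.
- Share of one arm exposed, p: 5%, 10% or 20% (assumption).
- Recording bias per exposed patient, b: 0.1 or 0.2 SD, all in one direction (assumption).
- Two-sided 5% comparison of means for these secondary outcomes (assumption).

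Formulas:
- SE of the difference = √(2/280) = 0.0845 SD.
- Bias in the arm mean = p × b.
- Rejection probability with no true difference = Φ(−1.96 + pb/SE) + Φ(−1.96 − pb/SE).

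| Share exposed | b = 0.1 SD | b = 0.2 SD |
|---|---|---|
| 5% | 5.04% | 5.2% |
| 10% | 5.2% | 5.6% |
| 20% | 5.6% | 7.6% |

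For the largest cell: pb = 0.20 × 0.2 = 0.04 SD, and 0.04/0.0845 = 0.473. Then Φ(−1.487) + Φ(−2.433) = 0.0685 + 0.0075 = 0.076.

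A harsher case, with 10% exposed and a bias of 0.5 SD each, gives pb = 0.05 SD and a rejection rate of about 9%.

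**The case against.** The strongest reply is that the Maintenance section asks for a number of patients and for reasons, not for a log of named patients. It does not say that the RAs obtain this by questioning patients during the outcome call. A tally supplied by the clinic, or taken after the questionnaires, would fit the wording. This stands in part: individual unblinding is an inference. It is a strong one, because reasons come from individuals and the RAs' stated follow-up contact is the telephone call.

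A second reply is that patients are told their own arm, so their self-reports are open to bias whoever asks the questions. That is true, and no change to the RAs' duties removes it. Interviewer blinding still protects against bias in prompting and recording, and that is the protection the protocol claims.

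A third reply is that question order and call scripts are operational detail that an article may leave to the full protocol. That is fair for scripts. It does not answer a conflict that the article itself states, with blinding asserted twice and the conflicting task given to the same staff.

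Two stronger readings are tempting. A reader might infer that assessor blinding does not exist at all. The text does not support this, because the task reveals nothing about patients who neither ask to change nor withdraw. A reader might also apply a bias of 0.1 or 0.2 SD to a whole arm and obtain false-positive rates of 22% and 66%. That arithmetic is correct (0.1/0.0845 = 1.18 and 0.2/0.0845 = 2.37), but it needs every patient in an arm to be affected, which this route does not produce.

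**Conclusion.** The point holds in a limited form. The protocol claims a blinding that its own Maintenance task very likely breaks for some patients at T2 and T3. The consequence is confined to three secondary self-reported outcomes; the primary HbA1c comparison is untouched. On the assumed range, the false-positive rate for an affected outcome moves from 5% to between about 5% and 8%. That rests on an assumed switching rate, an assumed bias per patient, and exposure in one arm in a single direction. The documents supply none of these. The case for changing the plan is that a stated safeguard is not fully in place and can be restored at almost no cost, not that a large error is expected.

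**What to change.** Have the clinic clerk, who already holds the group list and tells patients their allocation, record withdrawals, requests to change mode and the reasons at each timepoint. Remove this task from the RAs in the Maintenance section. The cost is a little clerk time.

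If the RAs must keep the task, they should take it only after the adherence, SF-12v2 and GP-visit items are complete for that timepoint. The blinding statements under Study setting and Data collection should then be qualified, because a change recorded at T2 may still unblind the RA for that patient at T3. For that reason the clerk is the better choice.
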